### Assignment of Groups

#### Allocation

A researcher who is not associated with this study and is not based at the study site will use a coin toss to randomize the wards included in the study to either the training intervention or the comparison group. This will occur once recruitment is complete. The first coin toss will identify which ward is being considered (ie, heads for one ward and tails for the other). The second coin toss will decide whether the selected ward is assigned to the intervention arm or to the comparator arm. Once the wards have been allocated, the study investigator will be unblinded and will individually notify participants via email regarding the arm of the study to which they have been allocated.

#### Blinding

Blinding for the study investigators and participants will not be possible. To reduce bias, once data are exported to Microsoft Excel, a researcher who is not involved with the study will code the intervention and comparator groups and remove data columns that relate to the intervention group only, so the person conducting the analysis will be blind to group allocation.

### Data Collection, Management, and Analysis

#### Overview

##### The Kirkpatrick Four-Level Model

The Kirkpatrick Model will be used to measure the impact of the training. This four-level model evaluates training according to (1) reaction, (2) learning, (3) behavior, and (4) results [28-30].

##### 1. Pre- and Posttraining Survey (Kirkpatrick Level 1)

A link to a short, electronic REDCap (Research Electronic Data Capture) survey will be administered to participants’ before and after simulation training, incorporating the Confidence in Coping with Patient Aggression Instrument [25], short-answer questions, and free text. These will be used to assess self-perceived levels of confidence and competence in managing aggression as well as the acceptability of the simulation and web-based training.

##### 2. Follow-Up Survey: 3 Months Posttraining (Kirkpatrick Level 1)

A link to a short, electronic REDCap survey will be emailed to participants 3 months after simulation training incorporating the Confidence in Coping with Patient Aggression Instrument [25], short-answer questions, and free text. These will assess self-perceived levels of confidence and competence in managing aggression as well as the acceptability of the simulation and web-based training.

##### 3. Observer Evaluation of Use of De-escalation Skills Within the Simulation (Kirkpatrick Level 2)

The simulation exercises will be recorded using Sportstec software. Sportstec is video analysis software designed for use in medical simulation research that allows users to interpret and code the multifaceted elements of video while identifying patterns that form a comprehensive picture. The video recordings are securely held on RCH servers and the software license includes use for research purposes. Two clinicians with expertise in the management of clinical aggression will assess the participants’ recorded performances for each scenario using the EMDABS [27,31]. The EMDABS is a one-dimensional, seven-item scale combined with a 5-point Likert scale ranging from 1 (*strongly disagree*) to 5 (*strongly agree*). Performance will be represented by the means of the seven items. The original German-language scale (De-escalating Aggressive Behaviour Scale, DABS) was enhanced and validated by Mavandadi et al [26] to create the EMDABS. This tool demonstrated good interrater reliability (intraclass correlation coefficient=.752) and strong internal consistency (Cronbach alpha=.901). Training materials have been provided by the authors of the EMDABS tool and will be used to train the clinicians in the use of the tool.

##### 4. Ward Patient Aggression Record (Kirkpatrick Level 3)

Episodes of clinical aggression from patients with ASD will be recorded during each shift in participating wards 1 month prior to and 3 months after the training intervention. Numbers of successful de-escalation interactions will be recorded. A short, electronic REDCap survey will be emailed to ANUMs, and to any additional nurses who acted in the role of ANUM, at the completion of the study to explore the enablers and barriers to collecting this data.

##### 5. Code Grey Activations (Kirkpatrick Level 4)

We will conduct a review of numbers and context of Code Grey activations in participating wards for 1 month prior to and 3 months after the training intervention. Strategies to be used by the study team to promote participant retention and completion of follow-up surveys are described in the Recruitment section.

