**Methods:**

This study has a mixed design, with between-group and within-participant comparisons to explore the acceptability and feasibility of delivering a large-scale cluster RCT. The trial process, including recruitment, completion rates, contamination, and completion of outcome measures, will be assessed and reported as percentages. This study will assess the acceptability of the simulation-based training format for two scenarios involving an adolescent with autism, with or without intellectual disability, who displays aggressive and externalizing behaviors and the resulting change in confidence in managing clinical aggression. Two pediatric wards of similar size and patient complexity will be selected to participate in the study; they will be randomized to receive either simulation-based education plus web-based educational materials or the web-based educational materials only. Change in confidence will be assessed using pre- and posttraining surveys for bedside nursing staff exposed to the training and the control group who will receive the web-based training materials. Knowledge retention 3 months posttraining, as well as continued confidence and exposure to clinical aggression, will be assessed via surveys. Changes in confidence and competence will be compared statistically with the chi-square test using before-and-after data to compare the proportion of those who have high confidence between the two arms at baseline and at follow-up. The simulation-based education will be recorded with trained assessors reviewing participants’ abilities to de-escalate aggressive behaviors using a validated tool. This data will be analyzed using mean values and SDs to understand the variation in performance of individuals who undertake the training. Data from each participating ward will be collected during each shift for the duration of the study to assess the number of aggressive incidents and successful de-escalation for patients with ASD. Total change in Code Grey activations will also be assessed, with both datasets analyzed using descriptive statistics.

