## Introduction

### Background and Rationale

Autism spectrum disorder (ASD), a neurodevelopmental disorder identified in childhood, is characterized by persistent deficits in social communication and social interaction across multiple contexts and restricted, repetitive patterns of behavior or interests [1]. Children diagnosed with ASD, with or without an intellectual disability, have an increased risk of hospitalization [2-5]. They also have longer and more frequent outpatient visits and medications prescribed than children in general [6]. Intellectual disability, one of the most prevalent comorbidities occurring in approximately 40%-70% of individuals with ASD [7-9], has been associated with greater autism symptomology with increased difficulties in communication and social functioning [10].

Exposure to the hospital environment can provide a sensory overload to children with ASD as it is often noisy and brightly lit, with people moving quickly, many unfamiliar people, and long wait times [11]. The surroundings are unfamiliar and usual home routines are not able to be maintained. The hospital environment necessitates that children must communicate with many more people, mostly unfamiliar, than usual. This is particularly challenging and stressful for children with ASD as they innately prefer less social interaction and have more difficulty identifying social cues and understanding the expressed emotions of others. Externalizing behaviors are common in children with ASD when exposed to these stressors and can result in difficult or delayed treatment, increased anxiety for the parent and child, prolonged procedure times, increased health care costs, and poorer health outcomes [2,6,11,12].

The Code Grey procedure is one of a series of emergency response codes used in some Australian hospitals. Code Grey refers to *unarmed aggression* and is called when an individual fails to respond to initial defusing mechanisms undertaken by staff [13]. At The Royal Children’s Hospital (RCH) Melbourne, the numbers of Code Grey activations are rising each year. In 2016, there were 611 recorded Code Grey activations, 1050 in 2018, and 1682 in 2019. In 2016-2017, 36% of Code Grey activations were due to aggression demonstrated by children and young people with ASD, with or without an intellectual disability [14].

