## Methods

### Participants, Interventions, and Outcomes

#### Study Setting

The study setting is a tertiary pediatric hospital, the RCH Melbourne, Australia. Recruitment will be performed from nursing staff from one general medical ward and one general surgical ward, both of similar size and patient complexity. Hospital data indicate that children and young people with autism, with or without intellectual disability, are admitted with similar frequency to these wards. The two included wards also experience similar numbers of aggressive incidents per year requiring a hospital Code Grey response.

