Each of the simulation training scenarios will be recorded. The recordings will be analyzed by two clinicians, who are experienced in clinical aggression management, using the EMDABS to assess the influence the training had on participants’ performances in de-escalating aggressive situations. A study investigator will train the clinicians in the use of the tool using the training materials provided by Mavandadi et al [26], providing a clear definition of terms and items and the scoring system. Both clinicians will use the tool on a recording of a practice simulation involving only members of the Simulation Faculty and the study investigator and will discuss decision-making processes to ensure consistency and interrater reliability [27].

Knowledge retention by study participants 3 months posttraining, as well as continued confidence and exposure to clinical aggression, will be assessed via surveys similar in content to the pre- and posttraining surveys. Results from the pretraining, posttraining, and follow-up surveys will be linked using the unique identifiers that the participants created prior to completing the pretraining survey.

Data will be collected at the ward level at each shift for the duration of the study to assess the number of aggressive incidents and rates of successful de-escalations for patients with ASD. A short survey will be emailed to Associate Nurse Unit Managers (ANUMs), as well as to any additional nurses who acted in the roles of ANUM or *nurse in charge of shift*, at the completion of the study to explore the enablers and barriers to collecting this data.

Total change in Code Grey activations will also be assessed in total and at the ward level. We will also record rates of data collection.

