## Results

This study gained ethical approval from the RCH Melbourne HREC on November 1, 2019 (HREC reference number: 56684). Data collection was completed in February 2020. Data analysis is due to commence with results anticipated by August 2020.

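### Code Greys are counted over 1 month before and 3 months after training but summarised as total change, so totals roughly triple under no effect; no ASD restriction is stated

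*Protocol article*

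**What the plan says.** Three places in the protocol article define the Code Grey outcome.

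- Section 5, Code Grey Activations (Kirkpatrick Level 4), sets the windows: a "review of numbers and context of Code Grey activations in participating wards for 1 month prior to and 3 months after the training intervention".
- The Outcomes section names the measure: "Total change in Code Grey activations will also be assessed in total and at the ward level". The abstract's Methods repeat it: "Total change in Code Grey activations will also be assessed, with both datasets analyzed using descriptive statistics".
- Statistical Methods, Secondary Outcomes, adds only that the analysis is descriptive, with an account of children who trigger more than one Code Grey.

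None of them gives a rate, a monthly mean or a denominator for Code Greys. The Outcomes section does speak of rates for successful de-escalations.

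The parallel ward record is restricted by diagnosis: "Episodes of clinical aggression from patients with ASD will be recorded during each shift in participating wards 1 month prior to" the training, and for 3 months after it. The Code Grey section states no such restriction.

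The Background gives the hospital-wide trend ("In 2016, there were 611 recorded Code Grey activations, 1050 in 2018, and 1682 in 2019") and says that 36% of activations in 2016-2017 were due to children and young people with ASD. The Study Setting says of the wards: "The two included wards also experience similar numbers of aggressive incidents per year requiring a hospital Code Grey response".

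**The concern.** A change in totals can be read only if the two totals come from equal observation time. Here the later window is three times the earlier one, so a change computed as named mainly reflects window length. Code Grey activations are the only Kirkpatrick level 4 result in the study. A tripling that is purely an artefact could be taken as harm, and a real fall in the monthly rate could be reported as a rise.

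The missing ASD restriction is a second, separate problem. The training is about children with ASD, and so is the ward record. If Code Greys are counted for all patients, most of the events may lie outside what the training addresses, and the level 3 and level 4 results will not describe the same population.

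**Working it through.** The article states no expected count or change for Code Greys, so there is no figure of its own to reproduce.

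**Inputs.** Windows of 1 and 3 months (section 5, Code Grey Activations). ASD share of 36%, hospital-wide, 2016-2017 (Background). Hospital totals of 611 in 2016, 1050 in 2018 and 1682 in 2019 (Background). No ward-level monthly count is given, so any such count below is an assumption.

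**1. Totals under no effect.** With a constant rate of λ per month, expected post/pre = 3λ/1λ = 3.0, a change of +200%. In calendar days the ratio lies between 90/31 = 2.90 and 92/28 = 3.29. For unchanged totals, the monthly rate must fall by 1 − 1/3 = 67%.

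**2. The same on a rate basis.** (3λ/3)/(λ/1) = 1.00. The artefact disappears.

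**3. Adding the document's own trend.** Growth from 2018 to 2019 is 1682/1050 = 1.602 per year. With r = ln(1.602)/12 per month, the ratio of totals is (e^(3r) − 1)/(1 − e^(−r)) = 3.25, or 3.25/3 = 1.08 per month of observation. At the 2016-2018 pace, (1050/611)^0.5 = 1.311 per year, the ratio of totals is 3.14. Trend is a small addition to the effect of window length, and this assumes that the hospital trend applies to these wards.

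**4. Between wards.** Assume no effect and baselines of 5 and 8 per month.
- Raw changes: 15 − 5 = +10 and 24 − 8 = +16, a spurious difference of 6.
- Ratio of ratios: (15/5)/(24/8) = 1.0. This comparison is not distorted.

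**5. All patients against ASD only.** Assume that the 36% share holds on these wards.
- Halving ASD-related Code Greys gives an all-patient rate ratio of 1 − 0.36 × 0.5 = 0.82 and a ratio of totals of 3 × 0.82 = 2.46.
- Abolishing them gives 1 − 0.36 = 0.64 and 3 × 0.64 = 1.92.

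So even the complete removal of ASD-related Code Greys would appear as nearly a doubling of the total.

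**6. Precision of the between-ward comparison.** Treat counts as Poisson, with the same monthly rate in both wards and periods. At an assumed 5 per ward per month, the SE of the log ratio of ratios is sqrt(2 × (1/5 + 1/15)) = 0.730, and the 95% CI factor is exp(1.96 × 0.730) = 4.2. The same formula gives 9.6 at 2 per month and 2.0 at 20 per month. That is a reason to keep this outcome descriptive.

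**The case against.** The strongest reply is that the article never says that raw sums over 1 and 3 months will be subtracted or divided. The word total may mean overall as opposed to by ward, and a fuller analysis plan could put the counts on a monthly basis. That stands as a limit on certainty. But the article does fix unequal windows and does name total change as the measure, and that pairing misleads if followed as written. The absence of a bed-day denominator would not by itself be a finding against an article.

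Second, both wards share the same windows. This stands: window length, and any season or trend common to both wards, cancels in the ratio of post/pre ratios. A reader might infer that every Code Grey comparison is biased; that is not so. However, the article does not name this ratio, and the change across both wards has no comparator. The Study Setting describes yearly numbers on the two wards as similar, which limits the spurious difference in raw changes but does not exclude it.

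Third, the planned review of context may allow ASD cases to be separated. It may, and that makes the remedy easy. The stated measure does not require it.

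Fourth, the outcome is secondary and descriptive, and the Secondary Objectives set its target as 80% reporting. This also stands and governs the severity.

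**Conclusion.** The point holds as a minor one. Taken as written, the plan gives a post/pre ratio of totals of about 3 under no effect, assuming a roughly constant rate and totals that are not standardised for time. Within-ward and overall changes in totals cannot be interpreted. Differences in raw change between wards are distorted when baselines differ; the ratio of ratios is not. That Code Greys cover all patients is inferred from the absence of a stated restriction and the contrast with the ward record. No feasibility criterion depends on the size of the Code Grey change.

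Three stronger readings are tempting but not supported.

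- A reader might infer that the windows could not be completed, because ethics approval came on November 1, 2019 and "Data collection was completed in February 2020". From November 1 to the end of February is 30 + 31 + 31 + 29 = 121 days, and 1 + 3 months is about 30 + 91 = 121. Recruitment could overlap the baseline month, and Code Greys could be extracted retrospectively. Truncation is not shown.
- A reader might want the baseline replaced by the preceding 12 months. On the 2018-2019 growth, the present window midpoints are 2 months apart, so trend alone gives 1.602^(2/12) = 1.08. A 12-month baseline puts them 6 + 1.5 = 7.5 months apart, giving 1.602^(7.5/12) = 1.34; the same months a year earlier give 1.60. That increases trend bias in the before-after comparison. Such data could at most be shown as background.
- A reader might call it an error that only 10 nurses per ward take part. The small trained share follows from pilot size, and the article states no expected ward-level effect.

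**What to change.** Replace total change with the following.

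- Code Grey rates per 30 days, by ward and period, using the actual start and end dates of each window. Show the counts and days alongside.
- For the ward aggression record, which uses the same unequal windows, rates per completed shift. Its denominator then also reflects missed shifts.
- A comparison of wards by their post/pre rate ratios, not by differences in raw change.
- ASD-related Code Greys as the main count, matching the training and the ward record, with all Code Greys as secondary.
- Description only, with no test.

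The windows need not change. The cost is a little extra tabulation, plus classifying each Code Grey by ASD status during the context review already planned. The article's Results section says that analysis had yet to start, so this could be settled before the data were analysed.

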#### Data Management

Participant confidentiality will be strictly held in trust by the study investigators and the sponsoring institutions. All surveys are anonymous so no personal details will be stored. The data from the EMDABS will be entered into a password-protected REDCap account by an administrative assistant. All survey data will be entered directly by participants into the secure REDCap web-based application. Sportstec recordings of the simulation-based education will be deleted once analysis is complete. All data for this study will be stored on a password-protected computer located in the Department of Neurodevelopment and Disability for 5 years. After 5 years, the data will be deleted.

#### Statistical Methods

##### Primary Outcomes

Percentages will be calculated to estimate recruitment, retention, outcomes, survey response rate, focus group participation, and the precision of those estimates. We will treat the Likert-scale scores as categories and dichotomize the 11- and 5-point scale responses. Changes in confidence and competence will be compared statistically with a chi-square test using before-and-after data to compare the proportion of those who have high confidence between the two arms at baseline and at follow-up.

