**Conclusions:**

We hypothesize that this study is feasible to be conducted as a cluster RCT and that simulation-based training will be acceptable for acute care pediatric nurses. We anticipate that the intervention ward will have increased confidence in managing clinical aggression in children with ASD immediately and up to 3 months posttraining.

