#### Outcomes

The primary and secondary outcome measures for assessing the acceptability and feasibility of conducting the training intervention are detailed in the Study Objectives section above.

Two simulation scenarios involving an adolescent with autism, intellectual disability, aggression, and externalizing behaviors will be assessed. Study participants will be asked to complete three surveys: a pretraining survey, a posttraining survey, and a follow-up survey.

The purpose of the pretraining survey is to determine participants’ self-perceptions of confidence and competence in managing aggressive and externalizing behaviors in a young person with autism. The pretraining survey incorporates the Confidence in Coping with Patient Aggression Instrument [25], short-answer questions, and free text to assess self-perceived levels of confidence and competence in managing aggression in a young person with autism and intellectual disability as well as acceptability of the simulation- and web-based education. The Confidence in Coping with Patient Aggression Instrument is a one-dimensional, 10-item instrument demonstrating a high degree of internal consistency (Cronbach alpha=.92) and precision (SE 1.5) [25].

The purpose of the posttraining survey is to determine if the training had an impact on participants’ self-perceptions of confidence and competence in managing aggression and externalizing behaviors in a young person with autism. The posttraining survey also incorporates the Confidence in Coping with Patient Aggression Instrument [25], short-answer questions, and free text to assess self-perceived levels of confidence and competence in managing aggression and externalizing behaviors in a young person with autism and intellectual disability as well as acceptability of the simulation- and web-based education. The purpose of the follow-up survey is to determine if the training had a continued impact on participants’ self-perceptions of confidence and competence in managing aggression in young people with ASD.

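### Confidence is tested between arms on dichotomized responses, with a baseline test and no deciding score, cut or survey; one total-score difference with an interval would serve better

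*Protocol article*

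**What the plan says.** The Primary Outcomes paragraph of Statistical Methods makes three commitments.

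- Scale: "We will treat the Likert-scale scores as categories and dichotomize the 11- and 5-point scale responses".
- Test: "Changes in confidence and competence will be compared statistically with a chi-square test".
- Contrast: the test is to "compare the proportion of those who have high confidence between the two arms at baseline and at follow-up".

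Other sections bear on how this is read.

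- Methods, Outcomes: the confidence measure "is a one-dimensional, 10-item instrument demonstrating a high degree of internal consistency (Cronbach alpha=.92) and precision (SE 1.5"). Participants complete "a pretraining survey, a posttraining survey, and a follow-up survey", so two of the three surveys come after training. Elsewhere the article uses the term follow-up survey for the 3-month one.
- Secondary Objectives: confidence and competence are secondary, judged by 80% of participants reporting an increase. No arm comparison or p-value is attached.
- Study Objectives, Outcomes: the feasibility criteria are rates (recruitment, attrition, acceptability, data collection, contamination). They accept a follow-up survey response as low as 30%.
- Sample Size: 10 nurses per arm. Study Purpose and Trial Design: two wards, so one per arm.
- Abstract, Conclusions: the intervention ward is expected to show "increased confidence in managing clinical aggression in children with ASD immediately and up to 3 months posttraining".

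**The concern.** The paragraph fixes a significance test but not what is tested. It does not say whether one classification per nurse or each scale response is dichotomized, where the cut for high confidence lies, or whether the immediate or the 3-month survey decides. The abstract anticipates a gain at both times. A secondary outcome's test also stands under Primary Outcomes, and nothing there labels it exploratory.

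Two features are weak on any reading. A significance test at baseline cannot show a training effect. Splitting a one-dimensional instrument into high and not high discards information that 10 nurses per arm can ill afford to lose.

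What is at stake is the reported confidence result. If several contrasts are available and one crosses 0.05, that one can be presented as bearing out the anticipated gain. According to the Results section, data collection had finished and analysis had not started, so these choices could still be fixed before anyone saw results.

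**Working it through.** The plan states no alpha, power or error rate, so there is no figure of its own to reproduce.

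**Inputs from the article.** 10 nurses per arm (Sample Size); 10 items with Cronbach alpha .92 (Outcomes); two post-training surveys (Outcomes); chi-square with no variant named (Statistical Methods).

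**Assumptions.** Two-sided 0.05; all 10 per arm respond; the true proportion with high confidence is the same in both arms, between 0.3 and 0.7; no ward effect; correlation between surveys 0 or 0.5. For the item-level reading, it is also assumed that the scale being dichotomized is the instrument's item format, which the article does not state outright.

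**Step 1: one score, one survey.** Summing the binomial probabilities of every 10 versus 10 table with p < 0.05 gives:

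| Test | True proportion 0.3 or 0.7 | True proportion 0.5 |
|---|---|---|
| Uncorrected chi-square | 3.7% | 4.2% |
| Yates or Fisher | 1.2% | 1.3% |

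**Step 2: one score, two surveys.** If the surveys were independent, uncorrected: 1 − (1 − 0.0371)² = 7.3% and 1 − (1 − 0.0422)² = 8.3%. With survey correlation 0.5 the simulated rate is slightly lower, so about 7-8%. With Yates or Fisher it is 2-2.5%.

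**Step 3: two scores (confidence and competence).** Simulated, uncorrected: 7-8% at one survey and 13-15% over two.

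**Step 4: ten items tested one by one.** The mean inter-item correlation implied by alpha is r = α / (k − (k − 1)α) = 0.92 / (10 − 9 × 0.92) = 0.92 / 1.72 = 0.535. Correlated latent normal items, dichotomized, in 20,000 runs, give the chance of at least one p < 0.05:

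| Setting | One survey | Two surveys |
|---|---|---|
| Uncorrected, latent r 0.535 | 26-29% | 44-50% |
| Uncorrected, latent r 0.745 (so that the dichotomized items correlate at about 0.535) | 22-24% | 37-42% |
| Yates or Fisher, latent r 0.535 | about 10% | 18-20% |

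These rates count differences in either direction. Differences favouring the intervention ward alone (uncorrected, r 0.535, survey correlation 0.5) are about half: 13-15% at one survey and 23-25% over two.

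**Step 5: cost of dichotomizing.** Assume a true difference of 1 SD, 10 per arm and no ward effect. A two-sample t-test on the score has power of about 56%. Cutting midway between the arm means gives proportions Φ(−0.5) = 0.309 and Φ(0.5) = 0.691, and the uncorrected chi-square has exact power of about 39%. The 1 SD is an illustration, not a figure from the article.

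**Step 6: which survey.** A 30% follow-up response meets the article's own criterion. If it applied evenly, 0.30 × 10 = 3 nurses per arm would be compared at 3 months.

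**The case against.** The strongest reply is that the text describes one comparison. The proportion concerns nurses, which suggests one classification each, and follow-up elsewhere means the 3-month survey, which leaves a single post-training contrast. On that reading the false-positive rate is about 4%, below nominal. This stands as a plausible reading, and it is why the larger figures can only be conditional. It does not settle the matter: the sentence before it dichotomizes scale responses, the instrument's total is never named, and the immediate gain anticipated in the abstract would then have no test.

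A second reply is that little turns on the test. This is a pilot, no feasibility criterion uses a p-value, and confidence has its own 80% criterion. That also stands and limits the consequence.

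A third is that cut-points and hierarchy may sit in a fuller protocol or analysis plan not shown. For a bare omission that would be enough. It does not answer the two choices the article does make, dichotomizing and testing at baseline.

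Finally, the Blinding section has the analyst work with coded groups. That limits choosing in a favoured direction but does not stop selection among items, cuts and surveys.

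A reader might infer that a false-positive arm difference is likely. The documents do not support that. The item-level figures need ten separate uncorrected tests, which the article nowhere states, and even over two surveys they do not exceed about 50%.

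**Conclusion.** The point holds in a limited form. The Primary Outcomes paragraph commits to a between-arm chi-square on dichotomized responses without saying which score, cut or post-training survey decides, adds an uninformative baseline test, and gives up information at 10 nurses per arm.

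With two-sided 0.05, uncorrected chi-square and no ward effect, the chance of at least one false-positive arm difference is about 4% (one score, one survey) or 7-8% (one score, two surveys). It is 26-29% or 44-50% only under item-by-item testing, and about 10% or 18-20% if those item tests use Yates or Fisher. Dichotomizing costs roughly 17 percentage points of power (56% against 39%) under an assumed 1 SD difference.

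The feasibility decision is unaffected. What is affected is how the anticipated confidence gain is reported. None of these figures allows for ward differences, which cannot be separated from training with one ward per arm.

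**What to change.** In Statistical Methods, Primary Outcomes:

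1. Name one arm comparison: the total score of the Confidence in Coping with Patient Aggression Instrument at one post-training survey. The posttraining survey is suggested because the plan accepts a 3-month response as low as 30%.
2. Report it as a difference with a 95% CI. State that, with one ward per arm, the interval reflects nurse-level variation only and cannot separate ward from training effects.
3. Report the other survey, the competence questions and any item-level or dichotomized results descriptively, labelled exploratory.
4. Drop the significance test at baseline.
5. Label the comparison as belonging to the secondary objective on confidence.

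The cost is a few sentences and no new data, since the items are already collected. The downside is fewer p-values, and the planned comparison of proportions becomes descriptive.
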